## Background

Transcatheter aortic valve replacement (TAVR) has become the preferred treatment option in patients with severe aortic stenosis (AS) [1–3]. However, experience with applying TAVR in patients with pure native aortic regurgitation (AR) is limited. A recent epidemiological survey showed a prevalence of moderate to severe pure AR as high as 1.2% in China, and it was found to be the most frequent type of valvular dysfunction [4]. Even though patients with severe AR and left ventricular ejection fraction < 30% have an annual mortality risk of 20%, only 5% of the patients have an operation because of the high risk [5]. It thus becomes imperative to determine whether TAVR could be a feasible option in poor surgical candidates. However, AR is usually associated with abnormalities of the aortic cusp or root, without valvular calcification. These distinctive anatomical characteristics are extremely challenging to deal with when anchoring the device in TAVR (Fig. 1). Several registries have recently reported unsatisfactory outcomes of TAVR in patients with pure AR. The 30-day mortality rate has ranged from 9.3 to 23%. A total of 7.5–27.3% of patients required a new pacemaker; 0–4.7% had a stroke; 20.9–23% had moderate to severe paravalvular regurgitation; and 0–24.4% of patients needed a second transcatheter heart valve (THV) [6–10].

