### Study end points

The study end points will be defined according to VARC-3 criteria [15]. The primary efficacy end point is the device success rate. The second efficacy end point is the composite of technical success and improvement in AR severity after the procedure. Furthermore, we will investigate several additional secondary end points, including the rate of rehospitalization for heart failure, change in functional capacity as indicated by whether the patient is rated as the New York Heart Association functional class I or II, the 6-min walk distances, and the plasma concentration of N-terminal fragment brain natriuretic peptides (NT-proBNP) at 12 months compared with baseline. We will also assess myocardial remodeling by determining changes in the echocardiographic parameters of left ventricular remodeling at 12 months, as well as the quality of life utilizing the Kansas City Cardiomyopathy Questionnaire (KCCQ) score.

The safety end points include the major adverse cardiovascular and cerebrovascular events, which are defined as the composite end points of death, stroke, myocardial infarction, renal failure, arrhythmia, and conduction block occurring after the puncture, and reoperation for device- or procedure-related adverse events. All-cause mortality (30 days, 6 and 12 months after the procedure), cardiovascular mortality (30 days, 6 and 12 months after the procedure), and the post-procedure rehospitalization rate due to heart failure (30 days, 6 and 12 months after the procedure). All primary and secondary end points and the relationship of the event to the device and to the operation will be determined by an independent clinical event committee based on the prespecified definitions after review of the original medical documentation. The details of the study end points are summarized in Table 2. Details of the assessment performed during hospitalization and at each follow-up visit are depicted in Table 3. Follow-up visits are planned at 1 month, 6 months, and 12 months for all patients after discharge, irrespective of whether devices are implanted. Collection of routinely available clinical data will be discontinued only if explicitly request by the subject.

**Table 2 Tab2:** Study endpoints

*Primary efficacy endpoint*

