Device success rate (at 30 days) according to VARC-3 criteria Technical success (at exit from procedure room) Freedom from mortality Successful access, delivery of the device, and retrieval of the delivery system Correct positioning of a single prosthetic heart valve into the proper anatomical location Freedom from surgery or intervention related to the device* or to a major Vascular or access-related, or cardiac structural complication Freedom from mortality Freedom from surgery or intervention related to the device or to a major vascular or access-related or cardiac structural complication Intended performance of the valve‡ (mean gradient < 20 mmHg, peak velocity < 3 m/s, Doppler velocity index ≥ 0.25, and less than moderate aortic regurgitation)
*Secondary efficacy endpoints*
Technical success rate
The rate of patients with AR ≤ 2 + after surgery (7 days after procedure/before discharge, 30 days, 6 months and 12 months)
The rate of postoperative hospitalization for heart failure (7 days after procedure/before discharge, 30 days, 6 months and 12 months)
The rate of NYHA class I or II after procedure (7 days after procedure/before discharge, 30 days, 6 months and 12 months)
Improvement of 6MWD from baseline (baseline and 12 months after procedure)
BNP/NT-proBNP improvement from baseline (baseline and 12 months after procedure)
Changes of echocardiographic LVEDV from baseline (baseline and 12 months after procedure)
Improvement of quality of life as assessed by the Kansas City Cardiomyopathy Questionnaire (KCCQ) score (baseline and 12 months)
*Safety endpoints*
Incidence of MACCEs during the study
Defined as the composite endpoints of death, stroke, myocardial infarction, renal failure, arrhythmia, and conduction block occurring after the puncture approach, and reoperation for device- or surgery-related adverse events
All-cause mortality (30 days, 6 and 12 months after procedure)
All-cause deaths include cardiac deaths, non-cardiac deaths, and unexplained deaths
Cardiac mortality (30 days, 6 and 12 months after procedure)
Post-procedure rehospitalization rate due to heart failure (30 days, 6 and 12 months after procedure)

**Table 3 Tab3:** Study data collection

Data collection	Baseline	Follow-up period				
		D1	D7/at discharge	D30	D180	D365
	− 7d	0d	0d	± 7d	± 15d	± 30d
Inform consent	X					
Demography	X					
Past history	X					
Vital sign	X		X	X	X	X
Physical Examination	X		X	X	X	X
History of angina	X		X	X	X	X
NYHA Functional Class	X		X	X	X	X

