### Statistical analyses

Data will be expressed as mean ± standard deviation for continuous variables and compared using the unpaired Student *t*-test or the Mann–Whitney U test. Categorical variables will be reported as numbers with the relative percentage and compared using the χ^2^ or the Fisher exact test as appropriate.

A recent meta-analysis [1] has reported a device success rate of TAVR for AR of 80.4% (95% confidence interval, 72.2–88.6%). According to the results of our feasibility study using this novel anatomical classification and dual anchoring theory, the expected device success rate of this study is set at 90%. Consequently, a minimal number of 86 severe pure AR cases at high risk for surgery is needed to appropriately answer the primary objective of the study. Our goal is to recruit 100 patients to account for 10% missing data or loss of patients to follow-up. A p-value of < 0.05 will be considered significant. Statistical analyses will be performed using the SPSS software (version 24.0) (IBM Corp., Armonk, NY, USA).

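### The last scheduled visit may fall on day 335, so events on days 336–365 may be missed from the 12-month mortality and heart-failure rehospitalization rates

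*Protocol article*

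**What the plan says.** Table 2 lists three safety endpoints at fixed times from the procedure: "All-cause mortality (30 days, 6 and 12 months after procedure"), "Cardiac mortality (30 days, 6 and 12 months after procedure") and "Post-procedure rehospitalization rate due to heart failure (30 days, 6 and 12 months after procedure"). Hospitalization for heart failure at 12 months also appears among the secondary efficacy endpoints.

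The last column of Table 3 is D365, with a window of plus or minus 30 days. Adverse events are recorded at each visit, and no visit or contact follows D365. The text under Study end points agrees on the number of visits but counts them from discharge: "Follow-up visits are planned at 1 month, 6 months, and 12 months for all patients after discharge, irrespective of whether devices are implanted". The next sentence adds: "Collection of routinely available clinical data will be discontinued only if explicitly request by the subject".

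For the analysis, the Statistical analyses section gives one general rule: "Categorical variables will be reported as numbers with the relative percentage and compared using the χ^2^ or the Fisher exact test as appropriate". The article describes no time-to-event method.

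**The concern.** One symmetric window serves two kinds of outcome. For a measurement such as echocardiography, 6-minute walk distance, KCCQ or NT-proBNP, a visit a month early or late does little harm. For an event rate fixed at 12 months, the early half of the window is different: the patient has met the schedule, yet the endpoint period runs on for up to 30 days with no planned check.

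If events are counted by date through day 365, an early last visit can only hide events. A patient last known alive on day 335 and counted in a plain percentage looks the same as one known alive on day 365. The study has no control arm that would share the same loss, so any shortfall makes the result look more favorable. It is also awkward to repair after close-out, because it would mean going back to patients or their records.

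**Working it through.** The document gives no figure of its own on this point, so there is none to reproduce. The check has two parts: which endpoints are exposed, and how large the loss could be.

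**Which endpoints are exposed** (windows from Table 3)

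| Endpoint time | Window | Earliest compliant visit | Next scheduled event check |
|---|---|---|---|
| 30 days | ± 7 days | 30 − 7 = day 23 | D180 |
| 6 months | ± 15 days | 180 − 15 = day 165 | D365 |
| 12 months | ± 30 days | 365 − 30 = day 335 | none |

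Events on days 24–30 and 166–180 can be picked up, with their dates, at the next visit. Events on days 336–365 have no later visit. The uncovered stretch is at most 30/365 = 8.2% of the period.

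**How large the loss could be**

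Inputs:
- Annual mortality. The Background section gives a figure for patients with severe AR and "left ventricular ejection fraction < 30% have an annual mortality risk of 20" percent. This describes a subgroup and is not a trial assumption; it is used here only for illustration. A range of 10% to 30% is assumed around it.
- Constant hazard over the year (assumed).
- Nothing learned after the last visit (assumed, worst case).

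Formula: daily hazard h = −ln(1 − m)/365 for true 12-month risk m. The risk observed to day 335 is 1 − exp(−335h) = 1 − (1 − m)^(335/365).

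At m = 20%: −ln(0.80) = 0.2231; 0.2231 × 335/365 = 0.2048; 1 − exp(−0.2048) = 18.5%. The shortfall is 20.0 − 18.5 = 1.5 points.

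For visits spread evenly, the shortfall is averaged over days 335 to 395, with zero shortfall from day 365 on. About half the patients are seen early, by 15 days on average, so the mean uncovered time is about 0.5 × 15 = 7.5 days.

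| True 12-month risk | Observed if all seen on day 335 | Shortfall, all on day 335 | Mean shortfall, even spread |
|---|---|---|---|
| 10% | 9.2% | 0.8 points | 0.2 points |
| 20% | 18.5% | 1.5 points | 0.4 points |
| 30% | 27.9% | 2.1 points | 0.5 points |

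In 100 patients at 20%, that is 1.5 deaths at worst and 0.4 deaths with an even spread. For comparison, the binomial standard error at 20% with 100 patients is √(0.2 × 0.8/100) = 4 points. The same arithmetic applies to a first heart-failure admission at the same assumed risks; the document gives no rate for it.

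**The case against.** Two stronger readings are tempting, and the document supports neither.

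A reader might infer that contact ends at the last visit and that events after it are definitely unobserved. The article does not say so. Collection of routine clinical data continues unless the patient objects, and deaths and heart-failure admissions are the kind of event such data can show. End points are also determined by an independent committee from the original medical documentation. Incomplete observation is therefore possible, not established. What remains is that the sentence on routine data names no date, no source and no duty to look. Across 14 centers, a death at home or an admission elsewhere need not reach the site's own records.

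A reader might also infer that the primary endpoint, "Device success rate (at 30 days) according to VARC-3 criteria", is exposed because the 30-day visit may fall on day 23. That does not follow. Adverse events are collected again at D180 and D365, and nothing in the article freezes the event components at the date of the 30-day visit.

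Three further objections deserve weight:
- The window also runs to day 395. If events were counted up to each patient's visit, late visits would add events and partly offset the early ones. The result would then be a rate over mixed follow-up lengths, which is still not the 12-month rate defined in Table 2.
- The full protocol or SAP, not shown, may set a censoring rule or a status check. Censoring would correct the estimate for shorter follow-up but would not recover events that nobody looked for. The window itself is stated in the article.
- Visits are counted from discharge in the text. On that reading the earliest last visit moves later by the length of stay. The gap narrows, but it closes only if the stay reaches 30 days.

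The effect is also small against sampling error, and this objection stands.

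**Conclusion.** The point holds for the 12-month event endpoints only: all-cause mortality, cardiac mortality and heart-failure rehospitalization. The stated schedule lets a compliant patient go up to 30 days of the endpoint period without a scheduled check, and plain percentages would not correct for it.

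The illustrative loss at 20% annual mortality lies between about 0.4 and 1.5 points, depending on when visits fall. It rests on a constant hazard, a mortality figure borrowed from a subgroup in the Background, and nothing being learned after the last visit. Any use of routine data would shrink it. The direction is toward fewer events, provided that events are counted by date through day 365.

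The 30-day primary endpoint, the 6-month events and the sample size are untouched. This is an inexpensive improvement to make before close-out. It is not a flaw that threatens the main conclusion.

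**What to change.** Keep the window of plus or minus 30 days for echocardiography, 6-minute walk distance, KCCQ and NT-proBNP. For the 12-month event endpoints, do one of the following:
- require vital status and heart-failure admissions to be confirmed on or after day 365 from the procedure, by telephone or record check for any patient seen early; or
- open the D365 window for events at 0/+30 days.

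In either case, state that events are counted by date through day 365 from the procedure, so that a late visit adds none from beyond 12 months.

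The cost is a footnote to Table 3, one short contact or record check for patients seen early, and a slightly later close-out for some of them.

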### Statistical analyses

Data will be expressed as mean ± standard deviation for continuous variables and compared using the unpaired Student *t*-test or the Mann–Whitney U test. Categorical variables will be reported as numbers with the relative percentage and compared using the χ^2^ or the Fisher exact test as appropriate.

A recent meta-analysis [1] has reported a device success rate of TAVR for AR of 80.4% (95% confidence interval, 72.2–88.6%). According to the results of our feasibility study using this novel anatomical classification and dual anchoring theory, the expected device success rate of this study is set at 90%. Consequently, a minimal number of 86 severe pure AR cases at high risk for surgery is needed to appropriately answer the primary objective of the study. Our goal is to recruit 100 patients to account for 10% missing data or loss of patients to follow-up. A p-value of < 0.05 will be considered significant. Statistical analyses will be performed using the SPSS software (version 24.0) (IBM Corp., Armonk, NY, USA).

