## Methods

The AURORA study is a prospective, multicenter, single-arm, cohort study that will be conducted in 14 high-volume centers with specified expertise in TAVR. Patients with symptomatic pure severe AR confirmed by an Echocardiographic Core Laboratory who are ≥ 65 years will be consecutively enrolled for multidetector computed tomography (MDCT) scanning. After discussions with the heart team, the patients who are considered to have a prohibitive or high risk for surgery will be classified into 4 types: types 1, 2 and 3 patients who have more than 2 anchoring areas for THV will be treated with the TAVR procedure, whereas patients classified as type 4 who have only 1 area [either at the left ventricular outflow tract (LVOT), annulus, or ascending aorta (AA)] or no suitable area for anchoring will continue to receive medical treatment. Procedural and 30-day, 3-month, 6-month and 12-month outcomes will be assessed according to the Valve Academic Research Consortium-3 consensus (VARC-3 criteria). Enrollment is expected to be completed within 18 months. Institutional ethical approval will be requested in each center according to local regulations that comply with the principles outlined in the Declaration of Helsinki for research in human subjects. The study flow chart is depicted in Fig. 2.

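### Mean ± SD is the only summary prescribed for continuous variables, NT-proBNP included, and neither named test analyses proportional within-patient change

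*Protocol article*

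**What the plan says.** The Statistical analyses section of the protocol article gives a single rule for continuous data. The summary is fixed first: "Data will be expressed as mean ± standard deviation for continuous variables". The same sentence then names the comparison: "compared using the unpaired Student *t*-test or the Mann–Whitney U test". The section names no median, quartiles, geometric mean or transformation, and no rule for choosing between the two tests.

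The natriuretic peptide is a named secondary efficacy endpoint. Table 2 lists "BNP/NT-proBNP improvement from baseline (baseline and 12 months after procedure". The Study end points text describes it as "the plasma concentration of N-terminal fragment brain natriuretic peptides (NT-proBNP) at 12 months compared with baseline". The Methods section describes the design: "The AURORA study is a prospective, multicenter, single-arm, cohort study". The comparison is therefore between two measurements on the same patients, not between two groups.

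**The concern.** Natriuretic peptides in patients with heart-failure symptoms are generally expected to be right-skewed and to change in proportion to their starting level. The article gives no NT-proBNP mean, SD or distribution, so this is an assumption here. If it holds, two things follow from the stated rule.

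- **Estimate.** The arithmetic mean at each visit, and the difference between the two means, depend heavily on the few patients with the highest concentrations. When the SD exceeds the mean, a mean ± SD display also spans negative concentrations.
- **Test.** Neither named test asks by what proportion a patient's own value changed. Both treat baseline and 12-month values as independent samples.

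At stake are an unstable, hard-to-read estimate for this endpoint and a real loss of power to detect a moderate fall.

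**Working it through.** The plan gives no NT-proBNP figure to reproduce. Its sample size of 86 (recruit 100) is for device success and does not enter this check.

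**Assumed inputs (none is in the article).** 80 patients with both measurements; log-normal values; the same log-SD, σ, at both visits; correlation ρ = 0.5 on the log scale; true geometric mean ratio 0.7 (a 30% fall); two-sided 5% tests; σ = 0.8, 1.0 or 1.2. Simulation used 5,000 replicates per setting, so the Monte Carlo standard error is at most √(0.25/5000) ≈ 0.7 percentage points.

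**Step 1: how skewed the assumed data are.** Raw CV = √(exp(σ²) − 1) = 0.95 / 1.31 / 1.79. Baseline mean minus one SD falls below zero in about 23 / 79 / 98% of simulated samples. The four most extreme of the 80 patients (5%) supply about 54 / 62 / 69% of the variance of the raw change.

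**Step 2: power for a 30% fall.**

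| Analysis | σ = 0.8 | σ = 1.0 | σ = 1.2 |
|---|---|---|---|
| Unpaired t, raw (named in the plan) | 74% | 41% | 23% |
| Mann–Whitney (named in the plan) | 86% | 62% | 42% |
| Paired t, raw differences | 88% | 62% | 42% |
| Signed-rank, raw differences | 94% | 80% | 65% |
| Paired t, log change | 97% | 88% | 75% |

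The last row can be checked without simulation. The standard error of mean log change is σ√(2(1 − ρ))/√80 = σ/√80 = 0.0894 / 0.1118 / 0.1342. With log 0.7 = −0.3567, the non-centrality is −3.99 / −3.19 / −2.66. The non-central t distribution with 79 degrees of freedom then gives 97.6 / 88.3 / 74.7%.

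**Step 3: separate pairing from scale.** From the unpaired to the paired raw t-test the gain is 88 − 74 = 14, 62 − 41 = 21 and 42 − 23 = 19 points; that is pairing. From the raw to the log paired t-test it is 97 − 88 = 9, 88 − 62 = 26 and 75 − 42 = 33 points; that is scale. Against a signed-rank test on raw differences, the log analysis still gains 3, 8 and 10 points, because ranks of raw differences are not ranks of ratios.

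**Step 4: does the rank test rescue the estimate?** This is a deliberate stress test on one simulated sample (n = 86, σ = 1.0, ρ = 0.5, true ratio 0.6). Baseline mean was 2375 and follow-up mean 1778, a ratio of 1778/2375 = 0.75. Multiplying the three largest follow-up values by 10 moved the follow-up mean to 6028, a ratio of 6028/2375 = 2.54. The Mann–Whitney p stayed at 0.0006, and was identical on the log scale; the unpaired t-test p went from 0.10 to 0.18. The p-value is protected, but the mean beside it is not.

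**The case against.** The strongest objection is that the plan names the Mann–Whitney U test. That test gives the same result on raw and log values and is barely moved by extreme values. A reader who stops at the first half of the sentence might infer that NT-proBNP will be tested on raw means, so that a handful of patients will decide the endpoint. The article does not support that: it assigns no test to NT-proBNP, and under the rank option extreme values do not decide the p-value. This part of the objection stands in full. A reader might also infer that the result could easily point the wrong way. Under the assumptions above, the raw mean rose despite a true 30% fall in only about 0.1 to 5% of samples, so that is uncommon.

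Two further points carry weight. The skewness is assumed, not documented. A condensed article also commonly leaves variable-by-variable choices of display, transformation and test to a fuller document that is not shown.

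What does not stand is that this disposes of the matter. The article is not silent: it states a rule for all continuous variables, with no exception. A rank p-value does not repair a mean ± SD estimate. Mann–Whitney's invariance to the log applies to the two sets of levels, not to within-patient changes, and its power here is about that of the raw paired t-test.

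**Conclusion.** The point holds in limited form. The article fixes mean ± SD as the sole summary for an endpoint that is probably skewed, and neither of its named tests analyses proportional within-patient change. Within the assumed range, log-scale paired analysis raises power from 86 / 62 / 42% to 97 / 88 / 75% against the better of the two named tests. Part of that is the benefit of pairing. The scale alone is worth 9 to 33 points against a raw paired t-test and 3 to 10 points against a signed-rank test on raw differences.

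These sizes rest on log-normality, ρ = 0.5, 80 pairs and a 30% fall, all assumed. With a larger effect or less spread the power gap narrows. The weakness of the mean ± SD display depends only on the skew. NT-proBNP is one of eight secondary efficacy endpoints in Table 2; device success, the primary endpoint, is a proportion and is unaffected. The change is worth making but does not threaten the main conclusion.

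**What to change.** Add an exception for NT-proBNP to the Statistical analyses section: analyse within-patient change in log NT-proBNP from baseline to 12 months with a paired method, and report the 12-month/baseline geometric mean ratio with its 95% confidence interval. Show median and quartiles at each time. Keep mean ± SD for variables that are roughly symmetric, which 6-minute walk distance and KCCQ score may be.

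The cost is a sentence or two of text. No extra data, visits or patients are needed, since both measurements are already scheduled in Table 3. If a fuller analysis plan already makes this exception, the article's general rule need only be aligned with it. The choice should be fixed before the 12-month values are examined.

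### The protocol names only tests for independent samples, but four secondary endpoints are within-patient changes from baseline to 12 months

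*Protocol article*

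**What the plan says.** The Methods section describes a "prospective, multicenter, single-arm, cohort study". Table 2 (Study end points) lists four secondary efficacy endpoints that compare a patient with himself or herself a year earlier:

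- Walking distance is entered as "Improvement of 6MWD from baseline (baseline and 12 months after procedure".
- The natriuretic peptide is treated in the same way, as "BNP/NT-proBNP improvement from baseline (baseline and 12 months after procedure".
- Ventricular volume follows the same pattern, as "Changes of echocardiographic LVEDV from baseline (baseline and 12 months after procedure".
- Quality of life also uses these two time points, with the instrument given as "Kansas City Cardiomyopathy Questionnaire (KCCQ) score (baseline and 12 months".

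The text under Study end points also describes its 12-month measurements as set against baseline. Table 3 schedules the 6-minute walk, NT-proBNP, KCCQ and echocardiography at both times.

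The Statistical analyses section gives one rule for continuous data: "mean ± standard deviation for continuous variables and compared using the unpaired Student". The alternative it offers is Mann–Whitney U. Its rule for the rest is "Categorical variables will be reported as numbers with the relative percentage and compared using the", followed by χ² and Fisher exact as the two options. The article names no paired test, signed-rank test or repeated-measures model.

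**The concern.** The only comparison stated for these four endpoints is baseline against 12 months in the same patients. The only tests named are for two separate groups of patients. The article has not merely left the test open: it specifies one and calls it unpaired.

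If an analyst follows the sentence as written, the two measurements on each patient are treated as if they came from different people. The part of the variation that cancels within a patient stays in the standard error. The stated 0.05 threshold then no longer corresponds to a 5% error rate, the confidence intervals are too wide when the correlation is positive, and a real improvement in function, biomarker, ventricular volume or quality of life is more likely to be missed.

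**Working it through.** The protocol gives no figure for the precision of these endpoints, so there is nothing of its own to reproduce. Its minimum of 86 patients was set for device success and is used here only as an illustrative n.

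**Inputs**
- n = 86 complete pairs (Statistical analyses).
- Significance level 0.05 (Statistical analyses). Sidedness is not stated; two-sided is assumed.
- 10% allowance for missing data or loss (Statistical analyses).
- Correlation rho between baseline and 12 months: not in the document, assumed 0.3, 0.5 or 0.7.
- True change of 0.3 SD: assumed, for the power illustration only.
- Equal SDs at both times: assumed, with SD set to 1.

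**Step 1: standard errors**
- Unpaired: √(2/n) = √(2/86) = 0.153.
- Paired: √(2(1−rho)/n), which gives 0.128, 0.108 and 0.084 for rho = 0.3, 0.5 and 0.7.
- Ratio, unpaired to paired: 1/√(1−rho).

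**Step 2: error rate and power (n = 86)**

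| rho | SE ratio | Actual type I error of unpaired t at nominal 0.05 | Power, paired | Power, unpaired |
|---|---|---|---|---|
| 0.3 | 1.20 | 0.021 | 64% | 50% |
| 0.5 | 1.41 | 0.006 | 79% | 50% |
| 0.7 | 1.83 | 0.0005 | 94% | 50% |

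The error rates and powers come from the t and noncentral t distributions. A simulation of 20,000 trials per rho agreed (type I error 0.020, 0.006 and 0.0006; paired power 64%, 79% and 94%). At rho = 0.5 the variance ratio is 1/(1−0.5) = 2, which is equivalent to discarding half the patients. These figures are for the t-test; no corresponding figures were computed for the Mann–Whitney test.

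**Step 3: the point estimate**

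With both values for every patient, the mean at 12 months minus the mean at baseline equals the mean of the individual changes. In the simulation the two never differed by more than 4 × 10⁻¹⁶, which is rounding error.

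The estimate moves only if the two means come from different sets of patients. Suppose a fraction d has a baseline value but no 12-month value, and these patients were D SD worse at baseline than the completers, whose baseline mean is m. The mean of all baseline values is then (1−d)·m + d·(m−D) = m − d·D. Comparing all baselines with the completers' 12-month values therefore adds an apparent gain of d·D. With d = 0.10:
- D = 0 gives 0
- D = 0.5 gives 0.05 SD
- D = 1.0 gives 0.10 SD

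D is an assumption.

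**The case against.** The best defence is that the sentence is generic. It ties the tests to no endpoint, and the study does contain independent groups: anatomical types 1 to 3, and type 4 patients on medical treatment, with follow-up planned whether or not a device is implanted. The named tests would suit two-group contrasts among these. That reading is possible, but no objective or endpoint states such a contrast, whereas the comparison with baseline is stated. Even on that reading, the four change endpoints have no suitable test among those named.

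It can also be said that an article leaves detail to a fuller analysis plan. That would answer a missing test. It answers less well a test that is named and does not fit. It does mean that one cannot say the analysis will be done wrongly, only that it would be if the text were followed.

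Three stronger readings are tempting, and the document does not support them:

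- **That the effect estimates will be wrong.** Choosing an unpaired test does not bias the mean change. Bias needs unequal patient sets, and nothing in the article says that all baselines will be compared with completers only. Larger shifts than those in Step 3 can be produced by borrowing the 9.3–23% mortality quoted in the Background, but that is 30-day mortality in earlier registries. The plan's own allowance is 10%.
- **That false positives result.** With positive correlation the error runs the other way.
- **That the NYHA endpoint has the same fault.** The text speaks of "change in functional capacity as indicated by whether the patient is rated as the New York Heart Association functional class I or II", which sounds like a change, but Table 2 clearly defines a rate of class I or II after the procedure. Such a rate needs no paired test, and requiring a one-class improvement would redefine the endpoint.

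**Conclusion.** The point stands for 6-minute walk distance, BNP/NT-proBNP, LVEDV and KCCQ: the tests named in Statistical analyses do not fit within-patient changes in a single-arm study. If they are used, standard errors are 1.20 to 1.83 times too large for rho between 0.3 and 0.7. P-values and intervals are wrong in the conservative direction, and power in the illustration is 50% instead of 64% to 94%. These sizes rest on assumed rho, equal SDs, complete pairs and, for power, a 0.3 SD change.

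The point estimate is sound on complete pairs. A shift of about 0.05 to 0.10 SD would need two conditions: all baselines compared with completers only, and the 10% lost being 0.5 to 1 SD worse at baseline.

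Device success, the primary endpoint, is a 30-day proportion and is unaffected. The severity is should-fix.

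**What to change.** Split the testing sentence in Statistical analyses in two:

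1. For endpoints defined as change from baseline to 12 months (6-minute walk distance, BNP/NT-proBNP, LVEDV, KCCQ), analyse the within-patient change with a paired t-test or, where the changes are clearly non-normal, a Wilcoxon signed-rank test. Report the mean change with its 95% CI in patients with both values, and state how many patients that is.
2. Keep the unpaired t-test, Mann–Whitney U, χ² and Fisher exact tests for comparisons between independent groups, such as anatomical types.

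Using patients with both values removes the risk of comparing different patient sets. It does not tell the reader how those lost would have fared, which is a separate missing-data matter for the full analysis plan.

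The cost is one paragraph. Table 3 already schedules the measurements at both times, and the sample size, visits and primary analysis do not change.
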